### Justification for choice of intervention and placental biomarker

As women with RFM are at increased risk of adverse pregnancy outcome, further tests are currently employed after a woman presents with RFM to identify fetal compromise using CTG, ultrasound assessment of fetal biometry and liquor volume, and fetoplacental Doppler studies [15]. However, this approach is based on low-grade evidence and further studies are needed [13].

As RFM is associated with abnormalities of placental structure and function [16], it was hypothesised that inclusion of placental biomarkers could improve identification of pregnancies ending in an adverse outcome. In recent years, interest in biochemical and sonographic markers of placental dysfunction, such as measurement of placental growth factor (PlGF) [26], hPL [27] and placental echotexture, has increased [28]. This is in part due to studies reporting low levels of placental biomarkers in placentally mediated pregnancy complications such as pre-eclampsia [29], FGR [30] and women perceiving RFM [27]. Cohort studies suggest that PlGF is able to differentiate between FGR secondary to placental insufficiency and constitutionally small for gestational age (SGA) fetuses, which would be advantageous as FGR infants are thought to be those at greatest risk of complications [26]. The levels of biochemical factors such as PlGF and hPL could reflect placental function as they are synthesised in the syncytiotrophoblast, the cell layer primarily responsible for nutrient and oxygen transport to the fetus. This hypothesis is supported by the observation that hPL levels correlate with placental size [27]. In a cohort study of 303 women with RFM, adverse pregnancy outcome was associated with an abnormal CTG, reduced fetal size, reduced liquor volume and lower levels of hPL [27]. Ultrasound estimated fetal weight predicted 20/67 (29.8%) infants with adverse pregnancy outcomes and hPL predicted a further 24/67 (37.8%). Therefore, combining estimated fetal weight and hPL identified a greater proportion of adverse pregnancy outcomes than ultrasound alone. A further study of women with RFM (*n* = 300) found a similar effect where addition of PlGF to standard ultrasound assessment improved the prediction of adverse outcome, with the area under the receiver operating characteristic (ROC) curve for composite adverse outcome improving from 0.75 (0.64–0.86) to 0.88 (0.80–0.95) and the sensitivity for adverse outcome improved from 9% (95% confidence interval [CI] 4–19%) to 38% (95% CI 21–57%) [31]. These data suggest adding measurement of placental biochemical factors to standard investigation regimes will increase the prediction of adverse outcome.

A systematic review of diagnostic test accuracy was carried out to determine the optimal marker of placental dysfunction from PlGF, hPL, oestriol and placental calcification (Heazell et al. submitted to Cochrane Database of Systematic Reviews; [32]). The diagnostic accuracy was compared to ultrasound biometry for the identification of stillbirth and SGA infants. This review found few high-quality studies which reported the combination of ultrasound estimated fetal weight and a placental biomarker, which is what is intended in ReMIT-2. Estimated fetal weight had the highest sensitivity for predicting an SGA baby (0.45, 95% CI 0.31–0.59). hPL performed better than oestriol or placental calcification with a summary sensitivity for detection of an SGA infant of 0.40 (95% CI 0.26–0.56) and a summary specificity of 0.86 (95% CI 0.77–0.91) in 3377 pregnancies. Four studies reported the ability of hPL to identify a pregnancy that would end in stillbirth. The sensitivity lies in the range of 0.63–1.00 and specificity of 0.56–0.86. There were three studies of PlGF in the prediction of an SGA infant, these reported a sensitivity in the range of 0.69–1.00 (592 pregnancies) and a specificity of 0.33–0.75. For stillbirth, PlGF reported a sensitivity of 0.88 and a specificity of 0.63 [32]. This suggests that PlGF has a slightly better test performance than hPL. Initial feasibility work has indicated that sites are either unable to perform hPL testing due to it being a time-intensive (up to 3 h) and resource-intensive test, or it is not practical to supply results within 24 h. Since the PlGF test is much quicker to perform and is not labour-intensive, PlGF is proposed as the biomarker of choice to assess placental function in ReMIT-2.

PlGF is bound in maternal blood by soluble-fms-like tyrosine kinase 1 (sFlt-1); therefore, assays to quantify PlGF measure either unbound PlGF or the ratio of sFlt-1 to PlGF. Comparison of these assays revealed no difference in their diagnostic performance [33]. The sFlt-1/PlGF ratio will be used in ReMIT-2 as it is a commonly available test in hospitals in the UK. An sFlt-1/PlGF ratio of ≥ 38 will be used as the threshold to identify significant placental dysfunction as this level increases the likelihood of delivery in women with suspected pre-eclampsia due to intervention to prevent maternal or fetal complications [34]. Before undertaking ReMIT-2, a diagnostic test accuracy study in 318 women presenting with RFM found that an sFlt-1/PlGF ratio of ≥ 38 had a sensitivity of 0.20 and a specificity of 0.88 to identify a composite adverse perinatal outcome (perinatal death, birthweight < 5th centile, umbilical cord pH < 7.1, admission to NICU for > 48 h; unpublished data). This compared to other methods employed, including oligohydramnios (sensitivity 0.12, specificity 0.85) or umbilical artery Pulsatility Index > 95th centile (sensitivity 0.05, specificity 0.95) and potentially represents a modest improvement in prognostic accuracy over ultrasound scan alone.

### Justification for qualitative study

Although little is known about women’s decision-making surrounding participating in clinical trials while pregnant, few clinical trials evaluate participants’ experiences to inform future trial design. In a follow-up questionnaire study conducted after the MAGPIE trial (a randomised controlled trial of magnesium sulphate to prevent eclamptic seizures), women were asked three questions to describe their experience of participating in the study [35]. Eighty percent of women responded and, in general, women were happy following participation in the MAGPIE trial and would do so again. Women made suggestions on how the trial may have been improved such as the timing and content of the participant information and wanting to know trial results. However, one difference between the MAGPIE trial and ReMIT-2 is that in MAGPIE, the main focus was maternal health as the women were unwell at the time of recruitment, whereas in ReMIT-2 the primary focus is on fetal wellbeing. In addition, ReMIT-2 is a ‘test-treat’ study rather than a trial of the effectiveness of an intervention. Thus, assessment of mothers’ experience is important in this pilot study as both of these differences may affect women’s perceptions of randomisation and participating in the study.

A recent qualitative study of women presenting with RFM demonstrated that presentation to the maternity service is a considered decision and for some respondents the prospect of intervention was a barrier to consultation [36]. Women were concerned for their baby’s wellbeing and sought investigation to confirm that their baby was healthy. This study highlighted powerful influences on women’s behaviour following perception of RFM. Thus, for future studies in this area, it is important to understand how participating in a randomised trial affects their experience of care. The Participant Views questionnaire being used in ReMIT-2 is adapted from that used in a single-centre feasibility study which achieved a 69% response rate [23] and includes questions initially described to evaluate the MAGPIE study [35].

As clinicians have a critical role in recruiting participants to clinical trials, their views and experiences will be recorded in this pilot study. In many studies, academic clinicians who initiate clinical trials are frequently not involved in recruiting participants. In their review of a maternity trial that did not meet recruitment targets, Costescu and Cullimore found that although all clinicians were able to identify eligible patients, only 60% had invited parents to participate [37]. Clinicians cited failure to consider trial participation and excessive clinical workload as the most commonly cited barriers to recruitment. They also identified a lack of personal incentive to recruit patients as a significant barrier. Thus, further exploration of the views of clinicians is needed to inform a definitive trial and for randomised controlled trials in maternity care as a whole.

Finally, it is important to gain further insight into how acceptable the sFlt-1/PlGF test is given the performance of this assay. Views will be gained from both women who do not consent to participate in the trial and those who do consent, along with the opinions of clinicians. The information obtained through this qualitative study will be used to inform the design of the large main trial.

### Objective

The overall objective of this trial is to assess whether for women with RFM, intervention directed by measurement of placental factors in addition to standard care improves pregnancy outcome compare with standard care alone. The aims of this pilot study are to determine whether a large main trial would be feasible and to provide proof of concept that informing care by measurement of the sFlt-1/PlGF ratio may improve neonatal outcome.

## Methods/Design

This is a multicentre, randomised controlled pilot trial of standard care informed by the results of an additional placental factor blood test versus standard care in women presenting with RFM at or after 36^+ 0^ weeks gestation.

### Participants

The flow of each participant from presentation through to follow-up is shown in Fig. 1. Inclusion criteria are women presenting with RFM before the onset of labour between 36^+ 0^ and 41^+ 0^ weeks gestation (assessment of gestation will be based on the best available information which will usually be the first or dating scan); viable singleton pregnancy on initial assessment; no indication for immediate delivery as assessed by CTG and ultrasound scan; provision of written informed consent. Exclusion criteria are maternal age < 16 years or > 50 years; fetus known to have any congenital anomalies as per the Fetal Anomalies Screening Programme (FASP) [38] or any other severe structural abnormality. Other exclusion criteria are multiple pregnancy; women for whom it is their first attendance to any antenatal care, e.g. ‘unbooked women’; previous randomisation into the ReMIT-2 trial in this pregnancy and concurrent participation in the intervention phase of another clinical trial which determined the timing or mode of delivery.

**Fig. 1 Fig1:**
[figure not shown]
Participant flow from presentation to follow-up. ^1^Participants in the control arm will have an extra blood sample taken to measure the sFlt-1/PlGF ratio but the sample ***will not be tested*** immediately so the result ***will not be available*** to site staff or the participant and therefore cannot be acted on. ^2^Discuss care being offered. Participants can decline or request delivery irrespective of the sFlt-1/PlGF result or the group they are randomised to

### Trial intervention

All participants will have a blood sample taken to measure the sFlt-1/PlGF ratio and will be randomised 1:1 to standard care with the blood sample tested locally at the time and the results revealed and acted on (intervention arm), or for the blood sample to be tested at a later time by a central NHS laboratory so the result is not available to site staff or the participant and therefore cannot be acted on (control arm; Fig. 1). Participants in the intervention arm with an sFlt-1/PlGF ratio ≥ 38 will be offered delivery at 37^+ 0^ weeks (or as soon as possible after 37 weeks) by the most appropriate method and induction of labour should commence within 48 h of this offer. Those in the intervention arm with an sFlt-1/PlGF ratio < 38 or those in the control arm will continue with usual care [9]. Participants in both arms will be free to decline the recommended management plan and may return for any further episodes of RFM before delivery but cannot be re-randomised into the trial.

### Outcome measures

Outcomes for the pilot trial have been separated into those that determine the feasibility of a definitive trial and those that address whether the intervention might have an effect on neonatal outcome or healthcare costs, i.e. proof of concept. The feasibility outcomes are: number of potentially eligible women at each site and number of women recruited at each site; proportion lost to follow-up after discharge from hospital and reasons for loss to follow-up; spectrum of clinical characteristics of women at randomisation (frequency of SGA fetuses, obstetric history, nulliparous); reasons for non-recruitment (including views of women about reasons for not participating collected at point trial is offered via an anonymous survey and a short interview); compliance with the trial interventions and reasons for non-compliance; completeness of data collection for planned outcomes in the main trial; participants’ views on the sFlt-1/PlGF test; views of women about participation collected after birth using a Participant Views questionnaire (modified from that used in the single-centre feasibility study [23]) and via an optional Midwife-Led Interview; views of clinicians on the sFlt-1/PlGF test performance, trial processes and interventions collected using a Health Professional Views questionnaire. The proof of concept outcomes for the mother are: frequency of induction of labour or planned Caesarean and reasons for these procedures; frequency of maternal hypertensive disorders defined as development of gestational hypertension or pre-eclampsia; maternal deaths before discharge or admissions to the intensive care unit (ICU); and change in the Generalised Anxiety Disorder 2 (GAD-2) scale [39]. For the baby. the proof of concept outcomes are: stillbirths and deaths before discharge; 5-min Apgar score of < 7; umbilical artery pH < 7.05; admission to the neonatal unit for > 48 h; SGA (< 10th centile on neonatal birthweight standards [40–42]); use of therapeutic cooling; length of stay in hospital; duration of respiratory support; and number of dependency days on the neonatal unit. The impact on quality of life and resource use will be assessed by the SF-12™ Health Survey [43], a Health Resource Use questionnaire and the diagnostic performance of the placental factor test in participants allocated to the control arm of the trial.

### Sample size and recruitment

As this is a feasibility trial, a formal sample size for estimating between-group effects is not appropriate. ReMIT-2 will recruit over a period of nine months from approximately six UK sites and it is expected that 175–225 participants will be recruited during this time. This number will give estimated margins of error (half width of 95% CI) for the proportion recruited of approximately 5% and for the proportion lost to follow-up after discharge of approximately 7.5%.

The maximum length of time from enrolment to delivery is six weeks. For participants not involved in the Midwife-Led Interview, the follow-up period from delivery to completion of the participant questionnaires is ~ 10 weeks. For the sub-group of participants involved in the Midwife-Led Interview, the follow-up period from delivery to completion of the interview is ~ 16 weeks.

### Enrolment and consent

As shown in Fig. 1, women presenting with RFM for the first time at or after 36^+ 0^ weeks gestation will have a pre-trial CTG to exclude fetal compromise along with an ultrasound scan for fetal biometry, liquor volume and umbilical artery Doppler. Once these investigations have been confirmed as normal and all eligibility criteria are met, written informed consent will be obtained. During the consent process, a Participant Information Sheet will be given along with a verbal explanation of the trial and standardised information on the test performance of the sFlt-1/PlGF assay in a visual format, e.g. DVD, YouTube, transcript, etc. (Additional file 2). The trial intervention means that ideally women need to be randomised on the same day that they present with RFM (or within the next working day); however, they will have the opportunity to ask questions and discuss their participation with others outside of the site research team. Although this is a limited timeframe, women in a prior feasibility study said that they felt the timing of the approach to offer participation was acceptable and that they had sufficient time to make a decision whether to participate [23]. Separate optional consent will be required for any participants who are interested in taking part in the Midwife-Led Interview.

Additional file 2:ReMIT-2 Participant Information Video MP4. (MP4 175104 kb)

Women who decline to take part will be asked if they are willing to complete an anonymous survey about their reasons for not participating in the trial (Fig. 2). At the Chief Investigator (CI) site only, this sub-group will also be asked if they are willing to have a short interview to further explore their reasons for not participating (Fig. 2). A separate Short Interview Consent Form will be completed before this interview is conducted. These interviews will last around 20 min and will be semi-structured using an Interview Guide but participants will be encouraged to speak openly and freely.

**Fig. 2 Fig2:**
[figure not shown]
Flow for women not giving consent to the trial

### Randomisation

Eligible participants will be randomised in a 1:1 ratio to either the intervention arm or the control arm. Randomisation will be stratified by site and number of weeks gestation when the participant first presents at hospital (< 40 weeks gestation or ≥ 40 weeks of gestation). The randomisation schedule is based on a computer-generated pseudo-random code using random permuted blocks of randomly varying size, created by the Nottingham Clinical Trials Unit (NCTU) in accordance with their standard operating procedure (SOP) and held on a secure University of Nottingham server.

Investigators and delegated site staff will randomise the participant using an online randomisation system via a secure website developed and maintained by NCTU. It is not possible to blind participants or site staff to the allocated arm since those randomised to the intervention arm will have the sFlt-1/PlGF ratio blood sample tested at the time and their results revealed to inform the next steps of their management plan. If a participant returns for a further episode of RFM, they will be treated according to standard care irrespective of the trial arm they were randomised to and will not have any further blood samples taken to measure the sFlt-1/PlGF ratio.

### Trial assessments and procedures

All assessments and procedures to be performed at each time point for participants are indicated in Fig. 3. Most assessments will be done at the time of enrolment and randomisation into the trial, including the SF12™ Health Survey and GAD-2 scale, demographics, medical history, concomitant medications, reasons for trial participation, physical examination, urinalysis and blood sample for the sFlt-1/PlGF ratio test. Further assessments will take place after delivery and before discharge from hospital including outcomes and defined serious adverse events (SAEs), demographics for the baby, Apgar scores, umbilical cord pH and base excess, neonatal unit admissions and details of any respiratory support. Participants will be followed up around six weeks after delivery via a Postnatal Questionnaire consisting of the SF12™ Health Survey, GAD-2 scale, Participant Views on the trial and Health Resource Use details. In addition, those participants that have given consent will be contacted for an optional Midwife-Led Interview.

**Fig. 3 Fig3:**
[figure not shown]
Summary of assessments. ^a^For stillbirths or deaths, the SF-12™, GAD-2, Health Resource Use and Participant Views questionnaires are only sent where the participant has confirmed they wish to continue in the trial. ^b^Midwife-Led Interviews are only to take place if the baby is still alive at the time of the interview, or for stillbirths and deaths where the participant has confirmed they wish to continue in the trial. ^c^sFlt-1/PlGF ratio blood test results will only be available at the time for participants in the intervention arm, not those in the control arm. ^d^For stillbirths and neonatal deaths prior to discharge, record cause of death, post-mortem findings and placental histology. Defined SAEs must be recorded from delivery to discharge from hospital for both the baby and participant. eDemographics e.g. gender, birthweight etc. ^f^Apgar scores to be recorded at 1 minute and 5 minutes after birth. ^g^For neonatal unit admissions, record reason for admission, duration of admission and number of dependency days

Before recruiting their first participant, staff at sites will be asked to complete part 1 of an online Health Professional Views questionnaire regarding the test performance of the sFlt-1/PlGF assays. Before closing recruitment, site staff will be asked to complete part 2 of the online Health Professional Views questionnaire regarding their experiences of the trial.

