### Adverse event reporting

Acting on the sFlt-1/PlGF ratio result is the intervention being evaluated and thus adverse events (AEs) are outcomes for the trial. Although stillbirths and deaths before discharge are outcomes for both the baby and the participant, these will still be considered as SAEs and will be reported as such.

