### Trial governance

The Trial Management Group (TMG) consists of the CI, Trial Statistician, Trial Manager and Senior Trial Manager. The TMG is responsible for the day-to-day management of the trial, including review of protocol deviations entered into the eCRF, and reporting to an independent Trial Steering Committee (TSC). Since the risk of adverse outcomes is deemed very low in this trial, a separate Data Monitoring Committee (DMC) has not been convened and therefore the TSC will also assume DMC responsibilities such as monitoring safety data and reviewing protocol deviations.

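### The defined-SAE window opens at delivery although the tested strategy acts before it, so some non-fatal antenatal and intrapartum SAEs need not be recorded in either arm

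*Protocol article*

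**What the plan says.** Four parts of the protocol article bear on safety recording.

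- **Fig. 3 notes.** "Defined SAEs must be recorded from delivery to discharge from hospital for both the baby and participant". This is the only recording window given for defined SAEs.
- **Trial assessments and procedures.** "Further assessments will take place after delivery and before discharge from hospital including outcomes and defined serious adverse events (SAEs"). This fixes when the assessment is made. It does not restrict when an event must have begun.
- **Adverse event reporting.** Because acting on the ratio is the intervention, "thus adverse events (AEs) are outcomes for the trial". The section then makes an exception: "Although stillbirths and deaths before discharge are outcomes for both the baby and the participant, these will still be considered as SAEs". No start at delivery is attached to it.
- **Outcome measures.** The maternal list includes hypertensive disorders and "maternal deaths before discharge or admissions to the intensive care unit (ICU"). The neonatal list includes stillbirth and death, low Apgar score, low cord pH, neonatal unit admission, cooling and respiratory support.

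Two sections give the timing of the strategy. Under Trial intervention, a woman in the intervention arm with a ratio of 38 or more is offered delivery at 37+0 weeks, or as soon as possible afterwards, "by the most appropriate method and induction of labour should commence within" 48 h of the offer. Under Sample size and recruitment: "The maximum length of time from enrolment to delivery is six weeks".

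Trial governance provides no separate data monitoring committee; "the TSC will also assume DMC responsibilities such as monitoring safety data".

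**The concern.** In a test-and-treat trial, exposure begins when the result is revealed. Waiting for delivery, the offer itself, induction and labour all come before birth. A window for serious events that opens at birth starts after the strategy has been carried out.

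Two things are at stake. First, a serious maternal event while waiting, or during an induction prompted by the test, may not be recorded if it is not fatal and is not on the outcome list. Second, the arms are meant to differ in time from randomisation to delivery for women with a raised ratio, so events before delivery are relevant to the comparison of the two strategies. A definitive trial, put in the Background at 5000 to 6500 women for the composite outcome, could inherit the same rule.

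**Working it through.** The plan gives no figure to reproduce here. The check sets the window beside the timing of the strategy and then asks which events are caught by another route.

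**Timing.** Enrolment to delivery can last six weeks: 6 × 7 = 42 days. That maximum does not describe women whose raised ratio leads to an accepted offer of delivery. For one of these enrolled at 36+0, the interval to 37+0 is 7 days, and induction follows the offer. In every case the time from randomisation to birth, including any induction, precedes the window.

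**Coverage of events with onset after randomisation and before delivery**

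| Event | Inside the Fig. 3 window, read by onset? | Caught elsewhere? |
|---|---|---|
| Stillbirth | No | Yes: reported as an SAE, and an outcome |
| Maternal death before discharge | No | Yes: reported as an SAE, and an outcome |
| Maternal ICU admission | No | Yes: outcome, with no start at delivery |
| Gestational hypertension, pre-eclampsia | No | Yes: outcome |
| Compromise in labour, baby born alive | Only as seen after birth | Largely: Apgar score, cord pH, unit admission, cooling, respiratory support |
| Other non-fatal serious maternal event while waiting, in induction or in labour | No | No |

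The last row is the gap. It applies equally to both arms.

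**Internal fit.** If the window is read by onset, a fetal death before birth lies outside it, yet Adverse event reporting makes stillbirth an SAE. If it is read as the time when forms are completed, stillbirth fits, but then the note says nothing about how far back onset may lie. On neither reading do the two sections together define the window.

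**Size.** The documents do not give the frequency of the unlisted events. The number of women offered delivery because of the test can be approximated. Under the justification for the biomarker, sensitivity is 0.20 and specificity 0.88. With prevalence p of that adverse composite, the share testing positive is 0.20p + 0.12(1 − p). Prevalence is not stated, so p is assumed to lie between 6% and 20%:

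- p = 0.06: 0.012 + 0.1128 = 0.125
- p = 0.20: 0.040 + 0.096 = 0.136

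The intervention arm has half of 175–225, or about 88 to 112 women. The expected number with a raised ratio is then 87.5 × 0.125 ≈ 11 to 112.5 × 0.136 ≈ 15. This assumes that the test behaves in trial entrants as it did in that study. Only a fraction of these women would have a serious unlisted event before birth. Such events can also occur in the remaining women of both arms.

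**The case against.** The strongest reply is that safety is handled mainly through outcomes, by design. Adverse event reporting says so, and Statistical analysis has outcomes summarised by allocated arm whatever the compliance. Harm while waiting would appear as stillbirth, pre-eclampsia or acidaemia, and harm to the baby from induction in the neonatal measures. Type of birth, and induction and planned Caesarean with their reasons, are also summarised. This stands, and it removes most of the larger concern.

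It is also fair to say that the note belongs to a figure that is not shown, that the list of defined SAEs is not in this condensed article, and that the note may describe when forms are completed. If the list holds mainly deaths and neonatal events, little is lost. The absence of the list is no fault of the article. But the note states a start point for both mother and baby, and a site following it literally would not record an earlier event.

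A reader might infer more: that everything before delivery escapes safety recording, that the comparison therefore counts harm on one side only, or that the TSC sees only part of the picture. The documents do not support this. The main antenatal harm, stillbirth, is expressly an SAE. The listed outcomes are not limited to onset after birth. Nothing under Trial governance confines the TSC to SAE forms. Nor can the loss be sized by the share of follow-up time that falls before delivery: that needs durations the documents do not give, and it measures time rather than events.

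**Conclusion.** The point holds in a narrow form. As written, the window opens after the strategy has acted. It leaves non-fatal antenatal and intrapartum SAEs that are not listed outcomes without a requirement to be recorded, in either arm, for up to six weeks per woman. It also does not fit the treatment of stillbirth as an SAE in the adverse event section.

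The number of missed events in 175–225 women is probably small, and no feasibility conclusion of the pilot turns on it. The conclusion rests on a literal reading of the note and on the defined SAEs including at least some non-fatal maternal events. The reason to act is that the correction is cheap and that the pilot is the template for a far larger trial.

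**What to change.** Reword the Fig. 3 note so that defined SAEs are recorded from randomisation until discharge from hospital after the birth, for participant and baby, with the date of onset. Naming the discharge after the birth avoids closing the window at an antenatal discharge. Bring the Adverse event reporting section into line, so that stillbirths and deaths fall within the same window. Have the TSC review these events by arm over the whole period. Trial assessments and procedures can keep its time of assessment: the form may still be completed after delivery and before discharge, provided it looks back to randomisation.

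The cost is a small amendment, one date field in the eCRF and a few more SAE forms across the sites. Where recruitment has begun, events already missed among enrolled women should be sought from their maternity notes.
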